## Abstract

**Introduction:**

Irritable bowel syndrome with constipation (IBS-C) is a common functional gastrointestinal disorder characterized by constipation, abdominal discomfort, and a substantial impact on patients’ quality of life. While acupuncture could be effective in treating general IBS, high-quality clinical evidence specifically supporting its efficacy in IBS-C remains limited. Our study aims to address this gap by evaluating the effectiveness and safety of electro-acupuncture in managing IBS-C symptoms.

**Methods:**

This a multicentre, randomized, double-blinded, sham-controlled trial. A total of 60 IBS-C patients are randomized to receive either electro-acupuncture (n = 30) or sham acupuncture (n = 30). Patients undergo a 2-week screening period, followed by 6 weeks of treatment (12 sessions) and 6 weeks of follow-up. From the beginning of the screening period to the end of the trial, patients are instructed to complete daily diaries recording bowel movement timing, stool consistency, straining severity, sensation of complete or incomplete evacuation, and the name and dosage of any medications taken. The primary outcome measure follows the FDA-recommended endpoint for IBS-C trials. Additionally, biological samples are collected to explore the potential mechanisms underlying the effects of acupuncture on IBS-C pathology.

**Ethics and dissemination:**

The protocol (version 1.4.4) has received approval from the Institutional Review Board of Nanyang Technological University (IRB-2023-451).

**Trial registration number:**

NCT06219707.

## Introduction

1

Affecting approximately 10% of the general population, irritable bowel syndrome (IBS) is one of the most common functional gastrointestinal disorders in clinical practice (1). As a subtype of IBS, studies suggested IBS with constipation (IBS-C) accounts for one-third of total IBS patients under the Rome IV criteria (2, 3).

As a disorder of gut-brain interaction, IBS-C patients continuously suffer from symptoms such as abdominal pain, bloating, and infrequent, hard, or lumpy stools. Furthermore, patients frequently suffer from psychological distress and co-morbidities such as anxiety and depression (4). These symptoms not only reduce patients’ quality of life, but also pose a significant healthcare burden due to frequent medical visits (5). Despite the availability of pharmacological and dietary interventions, many IBS-C patients experience recurrent symptoms and dissatisfied treatment effects, highlighting the need for additional therapeutic options (6).

Recent research suggests that alterations in gut microbiota composition, neurotransmitter metabolism, and short-chain fatty acid (SCFA) production may play a crucial role in the pathophysiology of IBS-C (7–10). The gut-brain axis, a bidirectional communication pathway between the central nervous system and the gastrointestinal tract, is thought to be dysregulated in IBS-C patients, contributing to abnormal gut motility, visceral hypersensitivity, and psychological comorbidities (10–13).

Given these multifactorial mechanisms, there is growing interest in exploring non-pharmacological interventions, such as acupuncture, to modulate the brain-gut axis and restore gut homeostasis (14). Evidence suggests that acupuncture may influence gut motility, reduce visceral hypersensitivity, and regulate neurotransmitter-related pathways, leading to the alleviation of both gastrointestinal and psychological symptoms in IBS-C patients (15, 16).

Several clinical trials have shown that acupuncture can alleviate global symptoms and improve quality of life (17, 18). However, acupuncture studies focusing on IBS-C are limited by methodological shortcomings, including insufficient IBS-C-specific outcomes, inadequate blinding protocols, and a lack of sham-controlled designs (19, 20). Consequently, the therapeutic effects of acupuncture on IBS-C, particularly its impact on gut microbiota composition and brain-gut interactions, are not well understood.

In this acupuncture trial, we aim to evaluate the efficacy and feasibility of electro-acupuncture (EA) for IBS-C. We hypothesize that EA would result in superior symptom improvement compared to sham acupuncture. Additionally, through the collection of biological samples during the trial, we are going to investigate changes in the gut microbiota composition and related metabolites to explore potential mechanistic links between EA interventions and clinical outcomes.

## Methods and analysis

2

### Study design

2.1

This pilot, randomized, double-blinded, sham-controlled trial is being conducted in Singapore since September 2024 (with the first patient enrolled). The study design strictly adheres to the principles of Declaration of Helsinki, Good Clinical Practice (GCP) guidelines, and mirrors STandards for Reporting Interventions in Clinical Trials of Acupuncture (STRICTA) guideline and the Consolidated Standards of Reporting Trials (CONSORT) statement, including the CONSORT-Outcomes 2022 extension (21, 22). The study lasts for a total of 14 weeks. All eligible patients first undergo a 2-week screening period, which includes providing blood samples for routine testing prior to enrollment. After the screening period, eligible patients are randomized in a 1:1 ratio to receive either EA or sham acupuncture over a 6-week intervention period, followed by a 6-week follow-up phase (Figure 1; Table 1). Sham acupuncture is selected as to offset the placebo effect of acupuncture, and there is no standard medication in treating IBS-C.

**Figure 1 fig1:**
[figure not shown]
Study flow.

**Table 1 tab1:** Schedule of study procedures.

Week	0	2	3	4	5	6	7	13
Visit	1	2–3	4–5	6–7	8–9	10–11	12–14	15
Eligibility assessment	✓	✓						
Informed consent	✓							
Baseline data collection	✓							
Concomitant drug record	✓	✓	✓	✓	✓	✓	✓	✓
Adverse effects assessment		✓	✓	✓	✓	✓	✓	✓
Physical examination and samples collection	✓	✓					✓	
Food frequency questionnaire (FFQ)	✓							
Short-form Wang Qi’s body constitution classification questionnaire (SF-CCMQ)	✓			✓			✓	✓
Questionnaires with psychiatric assessment	✓			✓			✓	✓
Intervention		✓	✓	✓	✓	✓	✓	

Patients are required to fill in their diaries daily from the start of the 2-week screening period until the end of the trial, recording the timing of bowel movements (BMs), stool consistency, degree of straining during defecation, sensation of complete or incomplete evacuation, and the name and dosage of any medications taken. Throughout the trial, patients are asked to avoid making significant lifestyle changes, such as initiating a new diet or modifying their exercise routine. Patients must discontinue any medications listed in the exclusion criteria before entering the trial. Concomitant medications that may affect IBS symptoms, such as antibiotics, antidepressants, probiotics, or herbal medicine, are prohibited for at least 1 month before the screening period. If a participant meets the inclusion criteria but needs to use medications due to a comorbid illness or changes in health status, it will be recorded in the case report form (CRF).

### Eligibility criteria and recruitment

2.2

Participants are included in the study if they meet the following inclusion criteria: (1) Fulfilment of the Rome IV criteria for IBS-C (23); (2) Age of 21 to 65 years (inclusive); (3) Weekly average of worst daily abdominal pain score of ≥3 (0–10 scale) for at least 12 weeks before the first visit and during screening period (24); (4) < 3 complete spontaneous bowel movements (CSBMs) per week for at least 12 weeks before the first visit and during screening period (24); (5) Written informed consent. Exclusion criteria include (1) Pregnancy or breast-feeding; (2) Medical history of inflammatory bowel diseases, carbohydrate malabsorption, hormonal disorder, known allergies to food additives, and/or any other serious diseases; (3) History of gastrointestinal tract segment removal or bariatric surgery for obesity; (4) Appendectomy or cholecystectomy within the past 2 months, or other abdominal surgeries within the past 6 months prior to trial enrollment; (5) Unstable medical conditions that could be associated with abdominal pain or discomfort and could potentially influence the assessments in this trial (e.g., chronic kidney disease, endometriosis, lactose intolerance); (6) Diagnosed with primary severe mental illness; (7) Patients who have received acupuncture treatment in last 3 months, or took concomitant medication with affect gastrointestinal motility or visceral sensation, such as antidiarrheal agent, antidepressant, narcotic analgesic, and anticholinergic; (8) Alcoholism or drug abuse in past 1 year; (9) Having needle phobia or allergy to acupuncture needle materials; (10) Antibiotics and probiotics/prebiotics usage in the previous month; (11) Participating in other clinical studies.

Participants are recruited from online platforms and Singapore hospitals [National University Hospital (NUH), NTU Lee Kong Chian School of Medicine (NTU LKC Medicine), Singapore General Hospital (SGH), and Tan Tock Seng Hospital (TTSH)]. Acupuncture interventions are conducted at the Nanyang Technological University (NTU) Chinese Medicine clinic, as well as at a collaborative Traditional Chinese Medicine (TCM) clinic at Kwong Wai Shiu (KWS) Hospital. This collaborative clinic, which has received standardized training provided by the NTU research team, is restricted from collecting or handling outcome data from patients except for safety-related purposes. Subject recruitment advertisements approved by the NTU Institutional Review Board (IRB) are placed on the social network platform and in the hospitals. Participants who are interested in the trial can contact the investigators by telephone, e-mail, or online registration. According to the inclusion and exclusion criteria, a standardized screening form is used to identify the potential eligible participants. Once a potential eligible subject is confirmed, an investigator communicates remotely with the subject, explaining the purpose, procedures, nature of the study, to arrange dates for the subsequent in-person meetings. All participants are informed that they are free to withdraw from the study at any time.

### Intervention and control

2.3

Each patient is scheduled for a total of 12 treatment sessions, 30 min for each session, 2 times a week over a 6-week period. The selection of acupuncture points is based on TCM theory and evidence-based clinical research (18). According to the TCM theory, the Spleen transforms the food digested by the Stomach into essences and helps to transport throughout the body, while the Liver ensures the smooth flow of Qi, modifies the activity of internal organs (Zang Fu), and is highly related to the emotional and psychological state. Therefore, most TCM experts agree that the weakness of the Spleen and Stomach is the basic pathogenesis of IBS. In IBS-C patients, the syndrome of dryness and heat in the intestines indicates a further imbalance in fluid metabolism (25). The principles of treatment for IBS-C are to regulate the Qi movement among the Liver and Spleen, soften stools, and promote BMs. The following eight acupuncture points are selected for treatment: Baihui (GV20), Toulinqi (GB15), Taichong (LR3), Zhangmen (LR13), Sanyinjiao (SP6), Zhongwan (CV12), Guanyuan (CV4), Tianshu (ST25), Zusanli (ST36) (Table 2; Figure 2).

**Table 2 tab2:** Depths and anatomical locations of acupuncture and sham points used in the study.

Acupoint/Sham-Acupoint	Depth	Location
GV20: Baihui	0.5–1 cun	On the head, 5 cun superior to the anterior hairline, on the anterior median line.
Sham Baihui		1 cun 22.5 degrees lateral (left side of patient) to the midline and anterior of Baihui.
GB15: Toulinqi	0.3–0.5 cun	On the head, 0.5 cun within the anterior hairline, directly superior to the centre of the pupil.
Sham Toulinqi		1 cun 45 degrees superior and medial of Toulinqi.
CV12: Zhongwan	0.8–1.5 cun	On the upper abdomen, 4 cun superior to the centre of the umbilicus, on the anterior median line.
Sham Zhongwan		1 cun lateral (left side of patient) of Zhongwan.
CV4: Guanyuan	0.8–1.5 cun	On the lower abdomen, 3 cun inferior to the centre of the umbilicus, on the anterior median line.
Sham Guanyuan		1 cun lateral (left side of patient) of Guanyuan.
ST25: Tianshu	1–1.5 cun	On the upper abdomen, 2 cun lateral to the centre of the umbilicus.
Sham Tianshu		1 cun lateral of Tianshu.
LR13: Zhangmen	0.5–1 cun	On the lateral abdomen, inferior to the free extremity of the 11th rib.
Sham Zhangmen		1 cun to the inferior of Zhangmen.
ST36: Zusanli	1–1.5 cun	On the anterior aspect of the leg, on the line connecting ST35 with ST41, 3 cun inferior to ST35.
Sham Zusanli		1 cun lateral of Zusanli.
SP6: Sanyinjiao	1–1.5 cun	On the tibial aspect of the leg, posterior to the medial border of the tibia, 3 cun superior to the prominence of the medial malleolus.
Sham Sanyinjiao		1 cun posterior of Sanyinjiao.
LR3: Taichong	0.5–0.8 cun	On the dorsum of the foot, between the first and second metatarsal bones, in the depression distal to the junction of the bases of the two bones, over the dorsalis pedis artery.
Sham Taichong		1 cun to the lateral of Taichong between the second and third metatarsal bones.

**Figure 2 fig2:**
[figure not shown]
Anatomical locations of acupuncture and sham points.

For the EA group, disposable acupuncture needles (0.30 mm in diameter and 25–40 mm in length) are inserted obliquely at a depth of 10–30 mm into scalp acupuncture points (Baihui, Toulinqi) or straightly into body acupuncture points (Taichong, Zhangmen, Sanyinjiao, Zhongwan, Guanyuan, Tianshu, Zusanli). EA is applied to the abdominal points using fast and dispersed waves through an electric needle stimulator (ES-160 6-channel electro-acupuncture device) for 30 min. The waveform frequency is set to 5 Hz, and the current intensity is adjusted based on the patient’s comfort level, with licensed TCM practitioners continuously monitoring and adjusting the intensity during treatment to ensure safety and efficacy. The alternating stimulation is believed to produce maximal biochemical responses in the brain (26).

For the sham acupuncture group, disposable acupuncture needles (0.30 mm in diameter and 25–40 mm in length) are inserted to the similar depth as in the EA group, but at sham acupuncture points (Sham-Baihui, Sham-Toulinqi, Sham-Taichong, Sham-Zhangmen, Sham-Sanyinjiao, Sham-Zhongwan, Sham-Guanyuan, Sham-Tianshu, Sham-Zusanli; Table 2, Figure 2). The sham acupuncture points are located 1 cun away from the actual acupuncture points. For acupuncture points along the midline, the sham acupuncture points are positioned 1 cun to the left of the actual acupuncture points (based on the patient’s perspective). The sham points are not acupuncture points nor located on meridians (27). Both the EA and sham acupuncture groups follow the same procedures, including connection to the stimulator device for the same duration. In the sham group, although no electrical current is delivered, the power switch is turned on and the knobs are manipulated to produce audible clicking sounds, mimicking auditory cues of active treatment.

### Outcomes and data collection

2.4

Daily symptoms recorded in physical or online patient diary include the number of BMs, SBMs, CSBMs, along with the severity of abdominal pain, discomfort, straining, and bloating, assessed using an 11-point scale (0 = none, 10 = worst possible). For each BM, stool consistency (7-point Bristol Stool Form Scale), sensation of severe straining during defecation, and use of medication are also recorded. Data will be entered electronically and stored in an encoded database within 24 h of receipt, with double data entry and range checks. Access to the trial dataset is restricted to investigators.

The primary outcome of the study is defined as responders who have a decrease in the weekly average of worst abdominal pain scores of ≥30% compared with baseline and a weekly increase of ≥1 CSBM from baseline (24). To assess the response over time, data between 2 groups will be summarized and compared throughout the treatment period and at the end of follow-up.

Other measurements include: (1) Proportion of patients with an improvement of ≥30% in abdominal pain scores from baseline; (2) Proportion of patients with an average increase of 1 or more CSBMs per week as compared with the baseline; (3) Average number of SBMs, CSBMs per week; (4) Percentage of bowel movements with normal consistency; (5) Percentage of bowel movements with severe or very severe straining during defecation; (6) Median time to the first SBMs, CSBMs after first session of EA; (7) Average number of bisacodyl tablets or enemas used per week; (8) Global assessment of efficacy of treatment with Likert scale at mid-treatment, end of the treatment, and end of follow-up; (9) IBS-C related severity and quality of life scores such as IBS Symptom Severity Scale (IBS-SSS), IBS Quality of Life (IBS-QOL), Patient Assessment of Constipation Symptoms (PAC-SYM), Constipation Quality of Life (PAC-QOL) and Patient Health Questionnaire-15 (PHQ-15) at the start of the treatment, mid-treatment, end of the treatment, and end of follow-up; (10) Depression, anxiety, and stress symptoms in IBS-C patients by Hamilton Depression Scale (HAMD), Self-rating Depression Scale (SDS), Patient Health Questionnaire (PHQ-9), General Anxiety Disorder (GAD-7), Hospital Anxiety and Depression Scale (HADS), Visceral Sensitivity Index (VSI) and Perceived Stress Scale (PSS) at the start of treatment, end of treatment, and end of follow-up; (11) Patient expectancy and trust in treatment, assessed via a brief questionnaire at the start of treatment, end of treatment, and end of follow-up; (12) Feasibility outcomes, including recruitment and retention rates, adherence to treatment protocols, completeness and quality of symptom diaries and questionnaire responses, and documentation of adverse events throughout the study. In addition to the primary and secondary outcomes, dietary intake and TCM constitutional patterns are assessed using the Food Frequency Questionnaire (FFQ) and Short-Form Wang Qi’s Body Constitution Classification Questionnaire (SF-CCMQ).

To facilitate participant compliance, several measures are implemented throughout the study. First, an informed consent process is conducted with all participants, providing information on the study schedule, potential side effects of treatment, participant responsibilities, and confidentiality, along with additional consent for collection and use of participant biological specimens (Supplementary File). Second, a 2-week screening period is conducted to identify and exclude ineligible or potentially non-compliant participants before randomization. Third, participants receive weekly reminders for upcoming appointments and the completion of their diaries. If a participant considers withdrawing from the study, the study team will engage with them to understand the reasons and explore possible solutions to address their concerns to retain the participant in the study.

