### Statistical analyses

2.9

All efficacy and safety analyses will be conducted based on intention-to-treat (ITT) principle. Missing values will be imputed by the last-observation-carried-forward method. Statistical analysis will be performed using the Stata software, with statistical significance defined as a two-sided *p*-value of <0.05. Baseline characteristics will be reported as mean (SD). Baseline differences between the groups will be evaluated using Student’s t-test for normally distributed continuous variables and the non-parametric Mann–Whitney U test for non-normally distributed variables. For categorical variables, the chi-squared test or Fisher’s exact test will be applied. Comparisons between groups will be conducted by using the unpaired t-test for normally distributed data and the Mann–Whitney test for non-normally distributed data. Within-group differences will be evaluated using the paired t-test for normally distributed data and the Wilcoxon signed-rank test for non-normally distributed data.

To minimize the risk of false positives, multiple-testing correction methods will be applied during the data analysis process where appropriate. Additionally, advanced statistical methods, including the Logistic Generalized Linear Mixed Model (GLMM), will be applied. Potential inter-center differences in study outcomes will also be assessed.

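### Time to first SBM/CSBM has no time zero for the sham arm, and the general analysis rules make no provision for patients observed without the event

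*Protocol article*

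**What the plan says.** Section 2.4 (Outcomes and data collection) lists as other measurement (6): "Median time to the first SBMs, CSBMs after first session of EA".

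Section 2.3 (Intervention and control) describes the control treatment: "In the sham group, although no electrical current is delivered, the power switch is turned on". Sham patients are needled at non-acupoints on the same schedule.

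Section 2.9 (Statistical analyses) gives rules for outcomes in general. On tests: "Comparisons between groups will be conducted by using the unpaired t-test for normally distributed data and the Mann–Whitney test for non-normally distributed data". Categorical variables get a chi-squared or Fisher's exact test. On missing data: "Missing values will be imputed by the last-observation-carried-forward method". It adds that "advanced statistical methods, including the Logistic Generalized Linear Mixed Model (GLMM), will be applied". No time-to-event method is named, and no test is tied to outcome (6).

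Three further passages bear on the point:
- Section 2.1 has all patients keep a daily diary from screening to the end of the trial, "recording the timing of bowel movements (BMs), stool consistency, degree of straining during defecation".
- Section 2.2 requires "< 3 complete spontaneous bowel movements (CSBMs) per week for at least 12 weeks before the first visit and during screening period", so a patient with none at all qualifies.
- Section 2.5 plans for 20% dropout.

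**The concern.** Two things do not fit together.

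First, the outcome is meant to compare two arms, but its clock starts at a treatment that only one arm receives. As worded, a sham patient's time cannot be computed.

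Second, time to a first event is incompletely observed for anyone who leaves, or reaches the end of observation, before the event. With entry at fewer than 3 CSBMs a week, zero included, and 20% dropout planned for, some such patients must be expected for CSBM. Neither the t-test nor the Mann–Whitney test has a built-in treatment of censoring. LOCF has nothing to carry forward for an event that has not happened. The analyst must improvise, and the possible improvisations give different answers. Patients without the event should be commoner in the arm that does worse, so leaving them out flatters that arm and narrows the difference.

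**Working it through.** **1. The plan's own figure.** Section 2.5: 70% v 30% response, two-sided alpha 0.05, power 80%, 20% dropout. With pooled variance:

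n = [1.96·√(2·0.5·0.5) + 0.842·√(0.7·0.3 + 0.3·0.7)]² / 0.4² = (1.386 + 0.545)² / 0.16 ≈ 23.3, so 24 per arm; 24/0.8 = 30 per arm, 60 in total.

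The stated N reproduces. It rests on the binary primary outcome, and nothing below changes it. The article states no figure for outcome (6).

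**2. Time zero.** Section 2.4 counts from the first EA session; section 2.3 gives the sham arm no current. The literal definition covers one arm. The diary records bowel-movement timing in both arms, so time from the first assigned session can be derived for every patient.

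**3. Effect on the median (assumed rates; the article gives none).** Let a patient's CSBM rate vary as a gamma variable with mean m per week and shape 1. Then the share with no event by week t is S(t) = 1/(1 + m·t). Take m = 1.0 (EA) and 0.5 (sham) and a 6-week window.
- No event by week 6, before dropout: EA 1/7 = 14%, sham 1/4 = 25%. With 20% dropout the simulated shares are 17% and 29%.
- Median with everyone kept, S(t) = 0.5: EA 1.0 week, sham 2.0 weeks; difference 1.0.
- Median among those with an event, before dropout. EA: S(t) = 1 − 0.5·(6/7) = 4/7, so t = 0.75. Sham: S(t) = 1 − 0.5·(3/4) = 0.625, so t = 1.2. The difference is 0.45 weeks; with dropout it is about 0.4.

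**4. Effect on power.** Simulation with the same means, 30 per arm, shape 1 or 2, and dropout times uniform over weeks 0.3 to 6. Ranges span repeated runs; the simulation error at 1,000 trials and 30% power is √(0.3·0.7/1000) = 1.4 points.

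| Handling of patients without the event | Dropout EA / sham | Power, shape 1 | Power, shape 2 |
|---|---|---|---|
| Dropped, Mann–Whitney | 20% / 20% | 15–18% | 24–25% |
| Last diary day as event time, Mann–Whitney | 20% / 20% | 29–31% | 41% |
| Ranked last, Mann–Whitney | 20% / 20% | 31% | 44% |
| Censored, log-rank | 20% / 20% | 29–32% | 43–45% |
| Last diary day as event time, Mann–Whitney | 10% / 30% | 22–24% | 34–36% |
| Censored, log-rank | 10% / 30% | 27–30% | 43–45% |

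**5. A second model.** Suppose a share q never has the event and the rest have rate 1 per week. The median over all patients is −7·ln[(0.5 − q)/(1 − q)] days. This gives 4.9, 5.7, 6.9, 8.8 and 12.5 days for q = 0, 10, 20, 30 and 40%. If patients without the event are dropped, it is 7·ln 2 = 4.9 days whatever q is.

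With q = 10% (EA) v 30% (sham) and 20% dropout, power is 4% (dropped), 22% (last day as event), 24% (ranked last) and 39% (log-rank). With q = 5% in both arms and rates 1 v 0.5 the four are close: 43%, 47%, 49% and 47%. In the equal-arm scenarios all four rejected in 4–6% of runs.

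**The case against.** The strongest reply is that the article fixes no method for this outcome. Section 2.9 is a general paragraph with an open list of further methods, and a full protocol or analysis plan may name Kaplan–Meier and log-rank. That stands. A reader might infer that Mann–Whitney with LOCF will be applied to outcome (6); the text does not say so.

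A reader might also infer that these tests cannot deal with patients without an event. For Mann–Whitney that is too strong: they can be ranked last when all are followed equally long, and under the gamma rates this matches log-rank. Nor does the article say that such patients are dropped or that the last diary day becomes their event time; its intention-to-treat statement argues against dropping them.

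The assumed rates may be pessimistic. Under shape 1 with mean 1.0, only e⁻¹ = 37% of EA patients have a rate of at least 1 per week, whereas section 2.5 expects 70% responders, each needing a gain of at least 1 CSBM per week. Means that put 70% v 30% at or above that rate solve e^(−1/m) = 0.7 and 0.3, so m = 2.80 and 0.83. The no-event shares at 6 weeks before dropout are then 1/(1 + 16.8) = 6% and 1/(1 + 4.98) = 17%. Diaries also run through follow-up: over 12 weeks the shares of 17% and 29% in the main scenario fall to 10% and 18%.

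Finally, the first EA session can charitably be read as the first treatment session. That is probably what was meant, but it is not what is written, and an unseen document does not correct a definition already published. What survives is the faulty time origin and general rules that, as stated, do not fit a listed outcome.

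**Conclusion.** The point holds as a definitional fault plus a conditional analysis risk. Time zero is undefined for the sham arm. The stated tests and LOCF rule make no provision for patients who drop out or finish observation without the event.

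A reader might go further and conclude that this outcome is distorted. The article does not support that, because the result depends on the share of patients without an event and on how they are coded, and it gives neither. Under the assumed gamma rates:
- **Material** for CSBM if they are dropped: power about 15% v 29%, sham median about 1.2 v 1.9–2.0 weeks.
- **Modest** if the last diary day is entered as the event time and dropout is unequal: about 23% v 29% (shape 1) or 36% v 45% (shape 2) at 10% v 30% dropout.
- **Negligible** with last-day coding and equal dropout. This is specific to those rates: in the never-event model last-day coding still lost power (22% v 39%).

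If nearly everyone has the event, the choice matters little. That is likely for SBM, since the entry limit concerns CSBMs only. The equal-arm runs gave no sign of excess false positives; the loss is in the reported median and in power. The primary outcome and N = 60 are untouched. Severity: minor, one secondary measure in a pilot trial.

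**What to change.** Reword outcome (6) as time from the first assigned treatment session (EA or sham) to the first SBM and, separately, to the first CSBM. Censor at the last diary day or at the end of a stated window, and say whether that window is the 6-week treatment period or the whole 12 weeks. Report Kaplan–Meier medians with 95% confidence intervals by arm and compare the arms with a log-rank test. State that LOCF does not apply to this outcome.

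The cost is a few sentences and a standard Stata analysis. The diaries already record the timing of bowel movements in both arms, so no new data are needed and the sample size does not change. The wording should be settled before unblinding.
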